### Secondary clinical outcomes

The secondary outcomes will be pain VAS at visit 12, Shoulder Pain and Disability Index (SPADI), range of motion (ROM), shoulder pain VAS while sleeping, blood stasis pattern identification questionnaire, and number of bands used per patients on each visit. All questionnaires will be presented in Korean.

#### Shoulder Pain and Disability Index (SPADI)

The SPADI questionnaire, assessing the pain and disability of shoulder joints, is composed of 5 items for shoulder pain and 8 items for shoulder disability to measure the shoulder mobility. Patients will check their discomfort by scoring each item from 0 to 10 [18, 19].

#### ROM of the shoulder

A goniometer (USA, iGaging, digital goniometer) will be used to measure the painful shoulders’ range of flexion, abduction, and internal and external rotation while the patients stand straight against the wall, and the sequence should be identical each time [20].

#### VAS of shoulder pain while sleeping

Patients will record the severity of their pain the previous night while sleeping by marking a vertical line on the VAS horizontal line.

#### Questionnaire based on blood stasis

Yang et al. [21] developed and verified the blood stasis questionnaire, including 14 articles (sprain, contusion, long-term numbness, tingling, pain in the lower belly, flank pain, nocturnal pain, feeling tumours in the abdomen, easily bruising, black face colour, blue or dark violet colour of the lips, tongue, gum, or eyelids, melena, and number of surgeries). Patients can express the strength of pain on a 7-point scale.

#### Number of bands used

Physicians will record the number of bands attached to each participant’s acupoints and the painful points of the shoulder on each visit.

### Other outcome measures

Feasibility outcomes of the study will include recruitment rate, completion rate and adherence to therapy. The ratio of included participants to all screened participants and the total enrolling target number will be presented as the recruitment rate. Therapy adherence will be shown as the percentage of each participant’s treatment frequency per total treatment frequency. Overall schedules of enrolment, interventions and assessments are shown in Fig. 4.

**Fig. 4 Fig4:**
[figure not shown]
Schedule of enrolment, interventions and assessments

### Sample size

No prior research has studied the effectiveness of taping therapy on controlling pain from shoulder arthroscopy. According to a recommendation report on pilot studies in the bioscience field, if there is no prior article from which to calculate the sample size of the study, the size could be 12 per group [22]. Thus, for this study, the intervention and control groups need 12 participants. Therefore, 15 participants per group are needed, considering a 20% dropout rate.

### Statistical analysis

#### Primary analysis group

When analysing the effectiveness of clinical trials, the primary analysis group will be the full analysis set group, and the per protocol group will be additionally verified. For safety analysis, the intention-to-treat analysis group will be the primary analysis group, and the per protocol analysis group will be additionally verified.

#### General rule of data analysis

All statistical analyses in the trial will be two-sided sets, and *p* values will be 5%. SAS^®^ Version 9.4 will be used to analyse the data.

#### Primary clinical outcomes

Mean VAS variation difference between visit 1 and 11 will be tested by the following hypothesis.

Null-hypothesis (H0): There is no difference in the mean VAS variation between before and after treatment in each group.

Alternative hypothesis (H1): There is a difference between the mean VAS variation before and after treatment in each group.

Mixed-effect Model Repeated Measures (MMRM) will be adapted for fixed factors, namely treatment groups and visiting time, while random factors will be the participants in the trial.

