**Fig. 1 Fig1:**
[figure not shown]
Appearance of Chimsband. **a** Individual Chimsband. **b** One set of Chimsband

This study is being conducted in order to explore the effectiveness and safety of Chimsband to control postoperative pain. The participants will be patients who have undergone arthroscopic shoulder surgery who have postoperative pain. This study will generate basic evidence on the effect of Chimsband and direct the topics of further studies. We hypothesise that treatment with Chimsband in addition to interferential current therapy (ICT) will be more effective than ICT treatment alone. We will test this hypothesis by a randomised controlled pilot trial. This study protocol was written in accordance with the Standard Protocol Items: Recommendations for Interventional Trials (SPIRIT). The SPIRIT checklist has been included in Additional file 1.

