### Interventions

The intervention group will receive ICT and additionally receive Chimsband therapy for 10 sessions over a period of 2 weeks. The control group will only receive ICT therapy. All intervention practitioners will not be involved in outcome assessment procedures.

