#### Secondary clinical outcomes

VAS at visit 11, SPADI, ROM, VAS while sleeping, questionnaire of blood-stasis pattern identification, and the number of used bands on visits 11 and 12 (secondary follow-up, fourth week from visit 1 with + 6-day window) will be analysed by the same method as in the primary effectiveness evaluation. For analysing the difference of measurement value between before and after treatment in each group, Student paired *t* test or Wilcoxon signed-rank test will be adapted for effectiveness evaluation variables. To test the difference related to variations of VAS per visit, repeated measures analysis of variance will be conducted, and the adjustment method of multi-comparison will be Dunnett’s procedure. In addition, the subgroups will be analysed depending on the pain severity or post-operation stage.

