#### Missing data

This study adopts the MMRM to analyse variations of evaluation parameters for the validity between groups. MMRM considers the missing values by maximum likelihood, not requiring any method of imputing missing values. Conversely, to reduce data loss, the missing values shall be substituted for the Last Observation Carried Forward method in case of adopting the Student paired *t* test (or Wilcoxon signed-rank test) to compare the pre- and post-treatment measurements in groups. Additionally, the Last Observation Carried Forward method shall replace the missing values in case if adopting the repeated measures ANOVA.

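### The primary null and alternative hypotheses are worded as before/after differences within each group, which contradicts the between-group trial hypothesis and the stated purpose of the MMRM

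*Protocol article*

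**What the plan says.** All references are to the protocol article.

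- **Statistical analysis, Primary clinical outcomes.** The section opens with "Mean VAS variation difference between visit 1 and 11 will be tested by the following hypothesis". The null hypothesis is "There is no difference in the mean VAS variation between before and after treatment in each group" and the alternative is "There is a difference between the mean VAS variation before and after treatment in each group". Neither sentence sets one treatment against the other. The model is an MMRM with "fixed factors, namely treatment groups and visiting time, while random factors will be the participants in the trial".
- **Background, last paragraph.** The trial hypothesis is that "treatment with Chimsband in addition to interferential current therapy (ICT) will be more effective than ICT treatment alone".
- **Missing data.** "This study adopts the MMRM to analyse variations of evaluation parameters for the validity between groups". The same section then turns to the paired t or Wilcoxon signed-rank test as the tool for comparing pre- and post-treatment values within groups.
- **Statistical analysis, Secondary clinical outcomes.** The within-group comparison appears as a separate analysis: "For analysing the difference of measurement value between before and after treatment in each group, Student paired" t test or the Wilcoxon signed-rank test. The secondary outcomes are otherwise to be analysed by the same method as the primary.
- **Interventions.** "The control group will only receive ICT therapy", so the control arm is actively treated.

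**The concern.** The trial is randomised to learn whether the tape adds anything to ICT. That is a question about the difference between two mean changes. The written hypotheses ask whether VAS changes from before to after treatment within an arm, which is what the supplementary paired tests address.

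Improvement in both arms is plausible without any tape effect. Both receive ICT, and all participants are selected on a screening VAS above 40, so some regression to the mean is possible. Rejecting the written null would therefore not show that Chimsband plus ICT is better than ICT alone.

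The stake is the meaning of a positive primary result. Someone who follows the hypothesis as printed could report success from a before/after change. Someone who follows the Background and the Missing data section would report success only from a difference between groups. The secondary outcomes inherit the ambiguity because they use the primary method.

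**Working it through.** **1. Passages side by side**

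| Place | Comparison stated |
|---|---|
| Background, trial hypothesis | Chimsband + ICT versus ICT alone |
| Primary outcome, null hypothesis | before versus after, in each group |
| Primary outcome, alternative hypothesis | before and after, in each group |
| Missing data, purpose of the MMRM | between groups |
| Missing data and secondary outcomes, purpose of the paired tests | before versus after, within groups |

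The primary hypotheses match the paired-test row, not the objective or the MMRM row. Null and alternative share the wording, so this is not a slip in one sentence. The model sentence lists group and visit as fixed factors. It does not say which estimate decides the primary question, so it does not settle the conflict.

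**2. The plan's own figure**

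Sample size section: 12 evaluable per group and 20% dropout. 12 / (1 − 0.20) = 15 per group, as stated. The 12 is a pilot rule of thumb, with no effect size, SD or power behind it. It therefore does not depend on which hypothesis is tested.

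**3. What the literal null would reject when the tape adds nothing**

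*Inputs from the document:* two-sided 5% level (General rule of data analysis); n = 12 evaluable or 15 enrolled per arm (Sample size).

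*Assumptions:* zero added Chimsband effect; the same true mean change in both arms, d, in units of the SD of change; normal changes; independent arms. The document gives no value for d, so a range is shown.

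*Formula for a paired t test in one arm:* noncentrality λ = d√n, degrees of freedom n − 1, and p = P(|T| > t(0.975, n − 1)), where T is noncentral t with parameter λ. For n = 12 the critical value is 2.201.

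Exactly one arm significant: 2p(1 − p). At least one: 1 − (1 − p)².

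| d (assumed) | λ, n = 12 | p in a given arm, n = 12 | exactly one arm | at least one arm | p in a given arm, n = 15 |
|---|---|---|---|---|---|
| 0.5 | 0.5 × 3.464 = 1.73 | 0.353 | 2 × 0.353 × 0.647 = 0.46 | 0.58 | 0.438 |
| 0.75 | 2.60 | 0.658 | 2 × 0.658 × 0.342 = 0.45 | 0.88 | 0.771 |
| 1.0 | 3.46 | 0.883 | 2 × 0.883 × 0.117 = 0.21 | 0.99 | 0.949 |

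By symmetry, half of the discordant results would favour Chimsband, for example 0.45 / 2 ≈ 0.22 at d = 0.75.

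**4. The between-group null under the same conditions**

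A two-sample t test on change was simulated with 20,000 runs at d = 0.5 and 1.0, for n = 12 and n = 15. It rejected in 4.8% to 5.1% of runs. The common improvement cancels, as it should.

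**The case against.** **The intention is clear.** The Missing data section assigns the MMRM to the comparison between groups and the paired tests to change within groups. The MMRM is the primary method and includes treatment group. This stands. A reader might infer from the printed hypotheses that the randomised comparison will not be tested at all. The document does not support that.

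**The wording may only be awkward English.** The article uses variation to mean change, so the alternative could be read as a difference between the groups' mean changes. That is a possible reading of the alternative. It fits the null less well, because there the two things compared are before and after. Evident intent explains the contradiction but does not remove it.

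**The trial is exploratory.** The article calls it exploratory and a pilot, and acknowledges the small sample. The hypotheses should not be called confirmatory, and the stakes are lower for it. Still, a formal primary hypothesis tested at 5% should be the one that answers the question.

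**The figures model another test.** They describe a paired t test, whereas the primary method is the MMRM, and the sizes of improvement are assumed. Participants may be up to 2 years past surgery with healed fixation, so marked natural recovery over about 2 weeks is not a given. This stands, and the figures are illustrations only. Nor are they inflated type I error rates: if both arms truly improve, the within-group null is false and rejecting it is correct. The trouble is that the rejection does not bear on Chimsband.

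**Misuse of within-arm p-values is speculative.** Nothing says that significance in one arm will be set against non-significance in the other. The discordance figures show what such a comparison would risk, not what is planned.

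**Some of the remedy is SAP detail.** The absence of a named contrast is not a fault on its own in a condensed article. Naming it is part of correcting a hypothesis that is stated wrongly.

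**Conclusion.** The concern holds as an internal contradiction. The primary null and alternative, read literally, are within-group statements. They conflict with the trial hypothesis in the Background and with the between-group role given to the MMRM under Missing data.

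On the literal wording, rejection is compatible with no added effect of Chimsband: about 35% to 88% in a given arm with 12 per arm, for an assumed common improvement of 0.5 to 1.0 SD of change. The size depends entirely on that assumption.

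The conclusion does not extend to a claim that the plan lacks a between-group analysis, or that the MMRM has an inflated error rate. The contradiction is still worth removing, because it determines what a positive primary result would mean.

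**What to change.** 1. Restate the null hypothesis: the mean change in VAS from visit 1 to visit 11 is equal in the Chimsband + ICT and the ICT groups. Alternative: the mean changes are not equal.
2. Say that it is tested by the between-group contrast at visit 11 (group-by-visit term) in the MMRM already planned, preferably reported with a 95% confidence interval.
3. State that the within-group paired t or Wilcoxon tests are descriptive and do not support a conclusion on the effectiveness of Chimsband.

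The cost is a few sentences in the analysis section, best settled before the data are analysed. Visits, data collection and the 15 per group are unchanged.

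Readers should know what the corrected test can deliver. For a two-sample t test on change, with noncentrality δ√(n/2) and 2n − 2 degrees of freedom, 80% power requires a difference of about 1.20 SD of change with 12 per group, or 1.06 SD with 15. That fits an exploratory trial and is a reason to lead with the estimate and its interval.

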**Methods/design:**

This is a randomised, parallel, controlled, exploratory clinical trial. Thirty participants who undergo arthroscopic shoulder surgery will be randomly allocated to an intervention or a control group. Both groups will receive 10 sessions of interferential current therapy within a period of 2 weeks, while the intervention group will additionally receive taping therapy after undergoing physical therapy. Two follow-up visits will be scheduled after the last treatment session. The primary outcome variable will be the difference in the visual analogue scale (VAS) scores between baseline and first follow-up evaluation after the end of 10 treatment sessions. The secondary outcomes will be VAS at the end of the second week, shoulder pain and disability index, range of motion, VAS while sleeping, questionnaire of blood stasis pattern identification at two follow-up visits, and number of bands used per visit. Outcomes will be evaluated at baseline, 2 weeks from visit 1 (+ within 6 days) after commencement, and at 4 weeks from visit 1 (+ within 6 days) follow-up.

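### Read literally, the primary model is a random-intercept model with no treatment-by-visit term, so the standard error of the visit 1 to visit 11 contrast can be wrong in either direction

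*Protocol article*

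**What the plan says.** In the Protocol article, Statistical analysis, Primary clinical outcomes, the target is introduced thus: "Mean VAS variation difference between visit 1 and 11 will be tested by the following hypothesis". The model follows: "Mixed-effect Model Repeated Measures (MMRM) will be adapted for fixed factors". The terms are then listed as "fixed factors, namely treatment groups and visiting time, while random factors will be the participants in the trial". No treatment-by-visit term and no within-participant residual covariance are named.

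Three other places bear on the point:
- The Abstract (Methods/design) gives the assessment times: "Outcomes will be evaluated at baseline, 2 weeks from visit 1 (+ within 6 days) after commencement, and at 4 weeks". That makes three: baseline, visit 11 and visit 12.
- Missing data relies on the same model for incomplete records: "MMRM considers the missing values by maximum likelihood".
- Secondary clinical outcomes applies the primary method to the secondary variables, so the specification carries over to them.

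The general rule is two-sided testing at 5%.

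**The concern.** A random participant effect with independent residuals has two variance parameters. It implies one variance common to all visits and one correlation common to all pairs of visits. The standard error for any change between two visits then comes from a single pooled within-participant error. That error averages the visit 1–11, 1–12 and 11–12 changes, although the primary question concerns only the first.

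Baseline precedes treatment and the two follow-ups come after it, so there is no particular reason for the three changes to be equally variable. If they are not, the primary p value and interval are miscalibrated. With 12 to 15 participants per group there is little margin. Likelihood handling of dropouts also depends on the covariance model.

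The missing interaction matters separately. With group and visit as main effects only, the model has no parameter for a between-group difference in change. If the groups are equal at baseline and differ by δ at both follow-ups, the group coefficient with complete data estimates (0 + δ + δ)/3 = 2δ/3, which is not the visit 11 effect.

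**Working it through.** **The document's own figure.** The only derived number is the group size: 12/(1 − 0.20) = 15. It reproduces. No SD, correlation, effect size or power is given, so all SDs and correlations below are assumptions.

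**Target.** The between-group difference in change from visit 1 to visit 11. The hypotheses in that section are worded within group, but Background states a between-group hypothesis and Missing data describes the MMRM as comparing groups.

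**Formula.** Take complete data and saturated group-by-visit means, which is more favourable to the plan than its listed terms. For T visits with covariance matrix S, the random-intercept model's expected residual variance is s² = (tr S − 1′S1/T)/(T − 1). It treats the variance of any change as 2s², which equals the average of Var(Yi − Yj) over all visit pairs. The true variance of the primary change is V(1,11) = S11 + S22 − 2·S12, with visits 1, 11 and 12 in that order. Hence

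model SE / true SE = √{[V(1,11) + V(1,12) + V(11,12)] / [3·V(1,11)]}.

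**Too small: follow-ups strongly correlated.** SDs 10/20/20, correlation between follow-ups 0.9.
- Baseline correlation 0.3: V(1,11) = V(1,12) = 100 + 400 − 120 = 380 and V(11,12) = 800 − 720 = 80. The mean is 840/3 = 280, so the ratio is √(280/380) = 0.86.
- Baseline correlation 0.5: the variances are 300, 300 and 80, with mean 226.7, so the ratio is √(226.7/300) = 0.87.
- Simulated type I error at this end is about 9% to 10%.

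**Too large: visit 12 more variable.** SDs 12/20/24, all correlations 0.5. The variances are 304, 432 and 496, with mean 410.7. The ratio is √(410.7/304) = 1.16 and type I error is 2.3%.

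**Too large: correlation decaying with time.** Equal SDs of 20, correlation 0.9 per week. V(1,11) = V(11,12) = 800(1 − 0.81) = 152 and V(1,12) = 800(1 − 0.6561) = 275.1. The mean is 193.0, so the ratio is √(193.0/152) = 1.13.

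**Baseline spread reduced, nothing else changed.** SDs 12/20/20, all correlations 0.5. The variances are 304, 304 and 400, with mean 336. The ratio is √(336/304) = 1.05, so the SE is slightly too large.

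**Simulated type I error** (two-sided 5%, 12 per group, 6,000 null trials per row):

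| Assumed covariance, visits 1/11/12 | SE ratio | Random intercept | Unconstrained |
|---|---|---|---|
| True compound symmetry, r 0.5 | 1.00 | 4.9% | 4.9% |
| Equal SD, decay 0.7 / 0.8 / 0.9 per week | 1.08 / 1.10 / 1.13 | 3.8% / 3.3% / 2.9% | 5.2% / 4.9% / 5.3% |
| SD 12/20/20, all r 0.5 | 1.05 | 3.9% | 5.1% |
| SD 12/20/24, all r 0.5 | 1.16 | 2.3% | 4.5% |
| Equal SD, baseline r 0.4, follow-up r 0.7 | 0.91 | 7.1% | 4.7% |
| SD 12/20/20, baseline r 0.4, follow-up r 0.7 | 0.95 | 6.5% | 4.9% |

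Monte Carlo error at 5% is √(0.05 × 0.95/6000) = 0.28 percentage points, so the unconstrained results of 4.5% to 5.3% are consistent with 5%.

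**Which visits enter also matters.** With visits 1 and 11 only, the ratio is 1.00 and type I error is 5.1%. If all 12 visits were modelled with decaying correlation, the ratio would be about 0.77 and type I error about 13%. The article mentions VAS by visit only for a separate analysis ("To test the difference related to variations of VAS per visit, repeated measures analysis of variance will be conducted"), so three assessments is the natural reading.

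**Degrees of freedom.** Random intercept: 2(n − 1)(T − 1) = 44 at n = 12 and 56 at n = 15. Unconstrained: 2(n − 1) = 22 and 28.

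**The case against.** The strongest reply is that the article never says participant is the only covariance component. MMRM normally means that the within-participant residual covariance is modelled, and calling participants the random factor may be shorthand for the repeated-measures subject. Covariance structure, degrees-of-freedom method and convergence fallback commonly sit in an analysis plan, which is not shown here.

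Part of that stands. The document does not rule out another residual structure, and silence on covariance alone would be no finding. But the article goes beyond the label: it lists the fixed factors and the random factor, and a programmer following that list would fit a random intercept without the interaction.

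Two stronger readings are tempting, and the document supports neither:
- A reader might infer that the standard error is necessarily too small and the primary p value too optimistic. The direction depends on SDs and correlations that the document does not give. The downward bias requires follow-ups that correlate clearly more with each other than with baseline. At SDs 12/20/20 and baseline correlation 0.5, the ratio is 0.96 with a follow-up correlation of 0.7 and already 1.01 with 0.6.
- A reader might cite the entry threshold of VAS above 40 as a cause of a too-small standard error. Reduced baseline spread alone moves the ratio up, to 1.05. The threshold also applies at screening, whereas the contrast starts at visit 1.

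Finally, this is an exploratory trial of 30 participants with no power calculation. That lowers the stakes, but the article still specifies a two-sided 5% test.

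**Conclusion.** The point holds in a limited, two-directional form. As written, the primary model is a random-intercept model without a treatment-by-visit term, and it can misstate the precision of the visit 1 to visit 11 between-group contrast. Over the assumed three-visit covariances, the model SE runs from about 14% too small (ratio 0.86, type I error about 9% to 10%) to about 16% too large (ratio 1.16, type I error about 2%). An unconstrained covariance holds about 5% throughout.

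These sizes rest on assumed SDs and correlations, complete data, saturated group-by-visit means, and baseline, visit 11 and visit 12 in the model. Sensitivity under dropout was not quantified. If the full plan already specifies an unstructured residual covariance and the interaction, only the article's wording needs correcting.

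**What to change.** State the primary model as follows:
- Visits 1, 11 and 12 are the repeated factor within participant, with an unstructured covariance in place of the random participant term.
- Treatment, visit and treatment-by-visit are fixed effects.
- Estimation is by REML with Kenward-Roger degrees of freedom.
- The result reported is the treatment contrast at visit 11 in change from visit 1, with its 95% CI.
- A fallback covariance is named in advance in case the model does not converge. Heterogeneous Toeplitz is one option, but over three visits it equates the 1–11 and 11–12 correlations. If it is used, a two-sample comparison of the visit 1 to visit 11 change should be shown beside it.

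The cost is a few lines of text and a change of SAS statement. The unstructured matrix has three variances and three correlations, which 24 to 30 participants can support. The downside is error degrees of freedom of about 22 to 28 instead of 44 to 56, hence a slightly larger critical value. The same wording should carry over to the secondary outcomes analysed by this method.

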### Randomisation and allocation concealment

A statistician not involved in the conduction and evaluation of the clinical trial will make the allocation list by block randomisation using Statistical Analysis System (SAS)^®^ Version 9.4 (SAS institute. Inc., Cary, NC, USA). The participants will be randomly assigned in a 1:1 ratio to the intervention group or control group. Participants who signed a written consent form will receive individual screening numbers. If the potential subject is eligible to participate in the clinical trial by screening, the statistician will allocate the randomisation numbers sequentially and finally determine the subject identification code. Once the number is allocated, reuse of the number is prohibited. If screened participants are not randomly allocated, the clinical research coordinator will record the individual numbers of participants not allocated and the reason patients were not allocated on the case report form.

Random allocation codes will be stored in opaque envelopes and kept in a double-locked cabinet. If the investigator decides to enrol a subject who signs informed consent and meets the inclusion/exclusion criteria, the investigator will open the randomised allocation envelopes in sequence with the participants and allocate subjects to each group. The investigator will record the opening date, sign the opened envelopes and store them separately.

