### Primary clinical outcomes

The primary outcome is shoulder pain and will be measured by the VAS measured at visit 11. If the score exceeds 40 points on screening, the participant will be enrolled in the study. Visit 11 will be at visit 1 + 2 weeks + 6-window days (last Chimsband attachment or ICT + 6-window days), as first follow-up date [16].

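### The primary mixed model uses baseline VAS only by subtraction, not as a covariate, which in a trial of about 12 evaluable per arm probably costs precision and leaves chance imbalance uncorrected

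*Protocol article*

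**What the plan says.** In the Protocol article, Statistical analysis, Primary clinical outcomes, the tested quantity is a change: "Mean VAS variation difference between visit 1 and 11 will be tested". The abstract agrees: "The primary outcome variable will be the difference in the visual analogue scale (VAS) scores between baseline and first follow-up evaluation". The Methods section on primary outcomes is worded differently, as a level rather than a change: "The primary outcome is shoulder pain and will be measured by the VAS measured at visit 11".

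The model is an MMRM with fixed factors and random factors listed as "namely treatment groups and visiting time, while random factors will be the participants in the trial". No baseline covariate is named there or elsewhere in the article. The section on secondary outcomes applies the same method to SPADI, ROM, sleeping VAS and the blood-stasis questionnaire, and adds that "the subgroups will be analysed depending on the pain severity or post-operation stage".

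Under Randomisation and allocation concealment, a statistician "will make the allocation list by block randomisation", with participants "randomly assigned in a 1:1 ratio to the intervention group or control group". No stratification factor is named.

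**The concern.** VAS at visit 1 is needed for the primary outcome, so it should be available for every participant analysed. Subtracting it is one way to use it. Fitting it as a covariate is another, and usually the more efficient one. With about 24 evaluable participants and no stratification factor named, nothing in the stated design or model corrects a chance difference between the arms at baseline.

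A change score does not remove such a difference. Unless the regression slope of follow-up on baseline is exactly 1, the arm that starts higher by chance will, through regression to the mean, appear to improve more or less than it should. The trial exists to give a first effect estimate that guides later studies, so both the precision of that estimate and its closeness to the truth in the one sample obtained matter.

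**Working it through.** **Inputs from the Protocol article.** 12 evaluable per arm, 20% dropout, 15 randomised per arm (Sample size); 1:1 allocation; two-sided 5% level ("All statistical analyses in the trial will be two-sided sets"); entry only with VAS above 40 at screening; surgery between 2 weeks and 2 years earlier.

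**Assumed, because the article gives no figure.** The correlation ρ between visit-1 and visit-11 VAS, and k = baseline SD / follow-up SD.

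**The plan's own figure.** 12 / (1 − 0.2) = 15 per arm. It reproduces. The 12 is a cited rule of thumb for pilot studies, not the result of a power calculation.

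**Step 1: chance imbalance.** The standardised baseline difference between two arms of n has SD √(2/n).
- n = 12: √(2/12) = 0.408. P(|difference| > 0.5 SD) = 2[1 − Φ(0.5/0.408)] = 0.22.
- n = 15: √(2/15) = 0.365, and the same probability is 0.17.

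**Step 2: what subtraction leaves behind.** For a baseline difference of d baseline SDs, the change-score contrast shifts by (ρ − k)·d follow-up SDs. With k = 1 and d = 0.5:
- ρ = 0.2: −0.40 SD
- ρ = 0.5: −0.25 SD
- ρ = 0.8: −0.10 SD

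**Step 3: precision.** In units of the follow-up variance, the per-arm variance is k² + 1 − 2ρk for the change score and 1 − ρ² for the baseline-adjusted analysis. Estimating the slope multiplies the latter by about 1 + 1/(2n − 4), which is 1 + 1/20 = 1.05 at n = 12. The ratio is

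1.05 × (1 − ρ²) / (k² + 1 − 2ρk).

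Example, k = 1 and ρ = 0.5: 1.05 × 0.75 / 1.00 = 0.79.

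| k | ρ = 0.3 | ρ = 0.5 | ρ = 0.7 |
|---|---|---|---|
| 1.0 | 0.68 | 0.79 | 0.89 |
| 0.8 | 0.82 | 0.94 | 1.03 |
| 0.7 | 0.89 | 1.00 | 1.05 |
| 0.6 | 0.96 | 1.04 | 1.03 |

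In the equal-SD row, 12 per arm work like 12/0.6825 = 17.6, 12/0.7875 = 15.2 and 12/0.8925 = 13.4.

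The loss has a limit. (k² + 1 − 2ρk) − (1 − ρ²) = (k − ρ)², which is never negative. Before the penalty, adjustment therefore cannot do worse than the change score. After it, the ratio cannot exceed 1.05, reached when ρ = k.

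**Step 4: detectable difference.** With k = 1, ρ = 0.5, 12 per arm and an assumed 80% power (noncentral t, two-sided 5%), the detectable difference falls from 1.20 to 1.06 SD.

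**Step 5: time since surgery as a second covariate.** Same setting. If it explains none, 10% or 20% of the residual variance, the detectable difference is 1.09, 1.04 or 0.98 SD, against 1.06 with baseline alone. The variance penalty with two covariates is 1 + 2/19 = 1.105, so break-even lies at 1 − 1.05/1.105 ≈ 5% of residual variance.

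**Step 6: subgroups.** If each arm of 12 split evenly in two, a comparison of 6 against 6 would need a difference of 1.80 SD for 80% power. The article gives no cut-points, so the even split is an assumption.

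**The case against.** Several points on the other side have force.

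- **Baseline is not ignored.** A reader might infer from the list of model terms that baseline VAS plays no part. The abstract and the statistical section do not support this: both define the outcome as change from visit 1. Only the Methods wording, which names VAS at visit 11, could be read that way. What is missing is the covariate.
- **The gain is not guaranteed.** A reader might also infer that adjustment must gain whenever the correlation is below 1. That needs equal SDs and ignores the cost of estimating the slope. The entry rule of VAS above 40 may well make the baseline SD smaller than the follow-up SD, and Step 3 shows the gain then shrinking or turning into a small loss. This stands, but the loss is capped at about 5% and the possible gain is several times larger.
- **The analysis is valid.** Under randomisation the unadjusted change-score contrast is unbiased on average. The imbalance argument concerns conditional bias in a particular sample, not a defect of the estimator.
- **Time since surgery.** The wide eligibility window makes it tempting to treat this as a strong prognostic factor. The article gives no figure for its strength or for the distribution that will be enrolled, so the window alone does not justify a place in the primary model.
- **A fuller plan may exist.** An article condenses, and listing factors does not strictly exclude continuous covariates. However, the article states the model terms itself, and a reader would take that list as complete.
- **The trial is exploratory.** It has no power target and acknowledges its small sample as a limitation. This bears on how serious the point is. It is not a reason to leave out a nearly free improvement.

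**Conclusion.** The point holds as a missed improvement, not as an error that invalidates the analysis. The stated primary model does not adjust for baseline VAS beyond subtracting it, and no stratification is named. With 12 evaluable per arm there is about a 22% chance of a baseline difference above 0.5 SD. At ρ = 0.5 and equal SDs, a difference of exactly 0.5 SD moves the contrast by 0.25 SD.

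With equal SDs, adjustment cuts the variance by about 32%, 21% and 11% at ρ = 0.3, 0.5 and 0.7. With a smaller baseline SD the gain is less, and the worst case is a loss of about 5%. All these sizes rest on an assumed correlation and SD ratio; the article supplies neither. No figure stated in the article becomes wrong.

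**What to change.** 1. In the primary MMRM, pre-specify visit-1 VAS as a covariate, with its interaction with visit. The treatment estimate is then the same whether the response is written as change or as VAS at visit 11, so the difference in wording between the sections can be settled without changing the result.
2. Do the same for SPADI, ROM and sleeping VAS, each with its own baseline.
3. Put time since surgery in a pre-specified sensitivity analysis, not in the primary model.
4. Present the subgroups by pain severity and post-operation stage descriptively.

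If the full analysis plan already contains the baseline covariate, confirming this is enough. The cost is a change of wording and code and one or two degrees of freedom. No new data are needed. The change should be fixed before outcome data are examined, which matters more than usual because the trial is open-label.
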